## **A 7.5 Study patients and schedule for inclusion**

The study will include 72 patients with CL coming from the State of Rio de Janeiro, attended at the Reference Center on Leishmaniasis - IPEC - Fiocruz.

As lesions located below the knee are expected to only be fully epithelized several weeks after the end of treatment, bias may occur in the assessment of treatment effectiveness if patients with this lesion location were more frequently present in a given treatment group. Likewise, patients older than 50 years usually present adverse effects more frequently and with greater intensity, and may negatively influence the safety assessment if they were present more frequently in a given group. These inclusion biases will be avoided through the strategy of block randomization and controlled with multivariate analysis, considering the following variables as potential confounders: age above and below 50 years and presence of lesions above and below the knees.

## **A 7.6 Outcomes**

### **A 7.6.1 Outcomes of Effectiveness: Definition**

1. Initial therapeutic response - presence or absence of total epithelization of all lesions until the consultation on day 120 (initial cure).

2. Late therapeutic response - presence or absence of the following elements in the progression expected for total healing:

- disappearance of crusts until the consultation of day 140;
- disappearance of desquamation (smooth surface) until the consultation of the day 230;
- disappearance of infiltration until the consultation of day 320;
- disappearance of erythema until the consultation on day 360 (definitive cure);
- no appearance of mucosal lesion until the consultation of day 770;
- reappearance of any stage previous to that achieved, maintained in 2 observations performed with an interval of at least two weeks.

### **A 7.6.2 Safety outcomes (adverse events): definition, strength and relationship to study drug**

An adverse event (AE) is any unanticipated or unfavorable event that either the investigator or the patient reports, starting during the use of the medication or within 30 days after its suspension. The AE examination will be made by spontaneous remembrance and questioned by the physician according to a standardized form on days 10, 20, 30, 50, 60 and 80.

The classification of the severity of adverse events (clinical, laboratory and electrocardiographic) will be given according to the tables in annexes 1 and 2 adapted from the "AIDS Table for Grading Severity of Adult Adverse Experiences, 1992" (Adult AIDS Clinical Trials Group August 1992).

The causal relationship with the study drug (= adverse effect) will be evaluated by the investigator and classified as follows:

1. Definitive (Highly Likely): A reaction that occurs within a reasonable time sequence after drug administration or when drug levels have established in body fluids and tissues; which follows a known standard response of the suspected drug; which is confirmed by the improvement after stopping the drug and reappears on repeated exposure.
2. Likely: A reaction that occurs within a reasonable time sequence after administration of the drug; which follows a known standard response of the suspected drug; which is confirmed by the improvement after stopping of the drug and which cannot be reasonably explained by the known characteristics of the individual's clinical condition.
3. Possible: A reaction that occurs within a reasonable time sequence after drug administration; following a known standard response of the suspected drug but which may be produced by the characteristics of the individual's clinical condition or other modes of therapy administered to the subject.
4. Remote (Probably Not): A reaction that occurs within a reasonable time sequence after drug administration; which follows a known standard response of the suspected drug but which can be reasonably explained by the characteristics of the individual's clinical condition.
5. Definitely No: Any reaction that does not meet the above criteria.

#### **A 7.7 Medication allowed during the test**

There will be no restrictions on the use of symptomatic medications and other diseases with the exception of those listed in the exclusion criteria (tuberculostatic, immunosuppressive and chemotherapy for cancer).

#### **A 7.8 Handling of adverse effects**

The AEs shall be recorded in an appropriate form, including: the description of the adverse effect, intensity, relationship to the investigated drug, date of onset, date of termination, duration and conduct taken.

As a general rule, appropriate measures will be taken to deal with AE described in this section.

### **A 7.9 Monitoring Parameters**

The effectiveness and safety parameters (outcomes) will be monitored according to the implementation schedule (item A 7.7).

Ascertainment biases will be minimized through the adoption of a standardized data collection form to be completed at each consultation by the team of trained professionals. This data sheet will include adherence data to the protocol, information on the periodicity of the correct (or not) administration of the drug, the collection of biological samples for exams and the occurrence of adverse effects and outcomes of interest.

### **A 7.10 Monitoring adherence**

Follow-up losses will be bypassed / minimized by active search: by telephone (two) and telegram (one) if no previous response is obtained. These features will be offered to all patients who miss a scheduled appointment. The patient will be asked to return the unused ampules, in order to account for the drug used.

### **A 7.11 Masking**

It was decided that a physician who was not aware of the therapeutic scheme would perform measurements of clinical (interest) and adverse (clinical) outcomes, in order to preserve masking between intervention and outcome. This step was taken to minimize the risk of ascertainment biases originated from differentiated outcomes according to the treatment scheme to which each patient belongs. The results of laboratory tests will be provided by the clinical pathology laboratory without information on the treatment group. Similarly, for analysis purposes, groups will not be identified. The database manager will preserve the confidentiality of this information by encoding the groups for analysis by the epidemiologist(s).

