### **A 7.3 Sampling plan**

#### **A 7.3.1 Sample size**

The groups with the minimum sample size (36 patients) are expected to respond to all the outcomes of interest.

We believe that the comparison of effectiveness between the two schemes will reveal non-inferior results to the alternative regimen for the following outcomes:

1. frequency of good initial response (evaluated on days 20, 30 and 50).
2. time (in days) until epithelization of all lesions is reached.
3. time (in days) to achieve total healing of all lesions.
4. frequency of good late response (one year of outpatient follow-up according to study schedule).

6. frequency of reactivation after treatment (up to two years of outpatient follow-up according to study schedule).

The significance level of 5% and power of 80% were used to calculate the required sample size to compare the frequencies of the outcomes of interest in the standard group with the other group. To test the non-inferiority between proportions in the primary endpoints of effectiveness, an acceptable limit of 15% difference between these healing ratios was considered. This will require 36 patients in each therapeutic regimen group.

Predicting the use of the McNemar paired test to compare the rates of healing or epithelialization on days 20, 30 and 50 will require at least 36 patients in each group (assuming a medically irrelevant difference of 30%).

To compare the effectiveness of treatment according to the location of the lesions, above or below the knee, only 12 patients will be needed in each treatment group.

It is expected that the alternative group (low dose, 5 mg Sb5+/kg/day) will present non-inferior results with a margin of 15%, and a lower frequency of clinical adverse effects, in addition to a low frequency of laboratory and electrocardiographic adverse effects. However, we expect to find a significant difference in the following outcomes when comparing the safety of the standard 20mg treatment with the alternative regimen:

1. frequency of clinical, laboratory or electrocardiographic adverse effects in any degree of intensity.
2. frequency of clinical, laboratorial or electrocardiographic effects of greater intensity.
3. frequency of treatment interruption caused by Adverse Events.
4. frequency of treatment dropouts.

In the case of elderly patients, a marked increase in the frequency and severity of AE in group 1 (20mg) is expected when compared to group 2 (5mg).

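### A 7.11 does not bring ECG reading or the causality call inside the masking, though the safety comparison counts ECG and drug-attributed adverse effects

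*Protocol*

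**What the plan says.** Three sections of the Protocol matter.

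- **A 7.11 (Masking)** names three masked steps. For clinical assessment, "a physician who was not aware of the therapeutic scheme would perform measurements of clinical (interest) and adverse (clinical) outcomes". For the laboratory, "The results of laboratory tests will be provided by the clinical pathology laboratory without information on the treatment group". For the analysis, "Similarly, for analysis purposes, groups will not be identified". ECGs are not mentioned, and in the first step the adverse outcomes are limited to clinical ones.
- **A 7.6.2 (Safety outcomes)** says of eliciting events: "The AE examination will be made by spontaneous remembrance and questioned by the physician according to a standardized form". It then says: "The causal relationship with the study drug (= adverse effect) will be evaluated by the investigator and classified as follows", followed by five categories from definitive to definitely not. It does not say whether this investigator is the masked physician of A 7.11. The section title places relationship to drug within the safety outcome: "Safety outcomes (adverse events): definition, strength and relationship to study drug".
- **A 7.3.1 (Sample size)** lists first among the safety outcomes expected to differ: "frequency of clinical, laboratory or electrocardiographic adverse effects in any degree of intensity". Specific objective 2 in A 6.2 likewise compares clinical, laboratory and ECG adverse effects.

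A 7.1 labels the trial double-blind. A 5.2 and A 9 state in advance that the 20 mg regimen is expected to be the more toxic.

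**The concern.** The safety comparison has three domains. Masked assessment is written down for two of them, clinical and laboratory, and not for ECG. A further step, the causality call, decides whether a recorded event becomes an adverse effect in the sense of A 7.6.2. That step goes to a person whose masking is not stated. For laboratory and ECG events, no masked person is assigned the call at all.

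If whoever grades an ECG or attributes an event knows the regimen and shares the stated expectation, more events could be graded or attributed as drug-related at 20 mg than at 5 mg even if the true event rates were the same. Coding the groups at analysis comes too late to correct a classification already made. What is at stake is whether a finding for the alternative safety hypothesis in A 5.2 reflects toxicity or partly reflects attribution.

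**Working it through.** **1. Masked steps against compared outcomes**

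| Step | Compared as a safety outcome? | Masking stated? |
|---|---|---|
| Clinical events, measurement | Yes (A 6.2, A 7.3.1) | Yes, masked physician (A 7.11) |
| Laboratory results | Yes | Yes (A 7.11) |
| ECG reading and grading | Yes | Not mentioned |
| Causality, clinical events | Yes, through the term adverse effect (A 7.6.2) | Investigator; masking not stated |
| Causality, laboratory and ECG events | Yes | Investigator; masking not stated |
| Group codes at analysis | – | Yes (A 7.11) |

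**2. Does the double-blind label settle it?** Not by itself. A 7.2 sets 20 mg for 20 days against 5 mg for 30 days, and no dummy or matched volume is described. Under A 7.16 a physician prescribes the medication. Under A 7.10 unused ampoules come back. Under A 7.9 one data sheet holds both drug-administration information and adverse effects. Some staff can therefore be expected to know the regimen, and masking depends on A 7.11 naming every step that needs it.

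**3. How much could it matter?** The plan gives no figure for this, so there is none to reproduce. The calculation below is illustrative.

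From the plan: 36 patients per arm (A 7.3.1). Assumed: a two-sided 5% Pearson chi-square test without continuity correction (A 7.17 names chi-square for healing frequencies and no test for safety frequencies); the same true proportion *p* of patients with an event in both arms; attribution shares *r*₁ at 20 mg and *r*₂ at 5 mg; and *k* events per affected patient, attributed independently.

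The proportion counted in arm *i* is *p* × [1 − (1 − *r*ᵢ)ᵏ]. For *k* = 1 this is *p* × *r*ᵢ. With *p* = 0.60 and shares 0.85 v 0.65, for example, it is 0.60 × 0.85 = 0.51 against 0.60 × 0.65 = 0.39. Summing the two binomial distributions over all tables that the test rejects gives the false rejection rate:

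| Attribution, 20 mg v 5 mg | Events per affected patient | *p* = 40% | *p* = 60% | *p* = 80% |
|---|---|---|---|---|
| 85% v 65% | 1 | 11.9% | 16.7% | 28.1% |
| 85% v 65% | 2 | 6.6% | 7.5% | 12.0% |
| 85% v 65% | 3 | 5.2% | 5.3% | 6.0% |
| 80% v 70% | 1 | 6.9% | 7.5% | 10.5% |
| 80% v 70% | 3 | 5.1% | 5.0% | 5.1% |

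With equal attribution and one event per affected patient, the same test rejects in about 4.5% to 5.4% of trials. In the 85% v 65%, one-event row almost all rejections point to more effects at 20 mg (at *p* = 60%, 16.5 of the 16.7 percentage points).

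**4. The same point in patients.** Starting from 10 v 10 patients with an adverse effect, moving four calls up in one arm and four down in the other gives 14 v 6 of 36: chi-square p = 0.035, Fisher exact p = 0.064. From 18 v 18, five calls each way gives p = 0.018 and 0.033. A few calls can decide the result. This does not show that they would be biased.

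**The case against.** A reader might infer that the ECG reader and the causality assessor are unmasked, and that the toxicity comparison as a whole rests on unmasked judgement. The document does not support either step.

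- **Nothing says that they are unmasked.** The trial is labelled double-blind, and the stated aim of A 7.11 is to keep assessment independent of the intervention. For clinical events, the masked physician may well be the investigator who completes the event form of A 7.8, where intensity and relationship to drug are recorded together. This stands: the text leaves the question open. It is weaker for laboratory and ECG events, where no masked person is named for the call.
- **Adverse effect may not always mean the attributed subset.** A 7.6.2 equates the two. But A 7.4.2 grades baseline abnormalities as adverse-effect levels, A 7.8 and A 7.12 mix the terms, and A 7.17 lists adverse events among the variables to be described. No cut among the five causality categories defines an attributed count. This also stands. It makes the size uncertain and is itself a reason to name the tested count.
- **Much of the safety assessment is protected.** Clinical measurement, laboratory results and analysis codes are masked, severity follows annexed tables, and A 7.3.1 counts interruptions on adverse events. This stands in part. Interruption is no complete safeguard, because A 7.12 ties definitive discontinuation to adverse-effect grade, ECG included.
- **The attribution shares are assumed**, and with several events per patient the inflation nearly vanishes, as the table shows. Nothing here quantifies the ECG half.

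**Conclusion.** The point holds as an incomplete masking rule, not as a demonstrated bias. A 7.11 sets out who is masked and leaves out ECG reading and grading and the causality classification, although both feed the safety outcomes that A 6.2 and A 7.3.1 compare. Because the regimens are distinguishable by dose and duration and the expected direction is written down, part of the toxicity comparison is open to directional judgement.

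The size cannot be fixed from the document. The false rejection rate runs from essentially nominal (about 5–6% with three independently attributed events per affected patient) to 28% (one event each, 80% of patients affected, attribution 85% v 65%). It depends on an assumed attribution gap and an assumed test. The non-inferiority comparison of cure is not touched by this point. Closing the gap is worth doing because it is cheap and removes a route for bias in the expected direction.

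**What to change.** 1. **A 7.11:** state that ECGs are read and graded under a code, without treatment group.
2. **A 7.11 and A 7.6.2:** state that the masked physician of A 7.11 records grade and causality for clinical, laboratory and ECG events.
3. **A 7.3.1:** make all-cause adverse event frequencies the between-arm comparison, with drug-attributed adverse effect frequencies as supportive. Use the two terms consistently and say which causality categories count as attributed.

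The cost is wording in three sections, plus coding of the tracings and some extra time for the masked physician. Sample size and treatment do not change. The downside is that all-cause counts include background events and are somewhat less specific. The event window of A 7.6.2 also runs 30 days past the last dose, so it is 20 + 30 = 50 days in one arm and 30 + 30 = 60 in the other when treatment is completed. An all-cause comparison should therefore state one common counting period for both arms.

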#### **A 7.12 Criteria for definitive discontinuation of study treatment**

1. interruption caused by clinical, laboratory or electrocardiographic AE Grade 4
2. interruption longer than 10 days due to clinical, laboratory or electrocardiographic adverse effects Grade <3
3. spontaneous interruption of the use of prescribed medication in an amount greater than five consecutive doses due to failure of administration (non-adherence)

#### **A 7.13 Criteria for withdrawal from the study (but not excluded from data analysis)**

1. definitive discontinuation of the treatment regimen for which it was randomized for any reason;
2. pregnancy;
3. need for introduction of immunosuppressive or potentially toxic drug (chemotherapy for cancer, tuberculosis or leprosy scheme);
4. Intercurrent disease, unrelated to the drug studied, but with manifestations equivalent or superior to clinical AD Grade 3;
5. need for re-treatment due to poor initial or late therapeutic response;
6. withdrawal of the patient from continuing in the study.

All patients will receive medical care at the leishmaniasis outpatient clinic of IPEC during the occurrence of adverse events. If necessary, the medication will be suspended for a maximum of 10 days and all affected patients will receive symptomatic treatment until the complete relief of the events temporally associated with the medication. They may have their treatment continued in an alternative regimen (but for the purposes of this clinical trial they will be analyzed by intention to treat, i.e. according to the group for which they were randomized). Whenever treatment is interrupted for safety reasons for more than 10 days, the patient will be withdrawn from the trial and restarted by intralesional treatment (subproject G).

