### **A 7.2 Description of the medication and schedule of interventions**

In Brazil, meglumine antimoniate (Aventis, São Paulo, Brazil) is stored at room temperature and distributed to the health network by the Health Surveillance Secretariat

- SVS / Brazilian Ministry of Health, which will provide a single lot to be used in all patients of the study.

This drug is for intramuscular (deltoid or gluteal) application in a single daily dose. Sterile plastic disposable syringes of 5 to 20 mL and disposable, sterile 25 × 7 mm needles will be employed.

The study using the intramuscular (IM) route without direct supervision will allow the evaluation of its use in real-world conditions (effectiveness) employed by the primary health services in the state of Rio de Janeiro. Although intravenous prescription is possible, it is not a usual route of antimony administration and it is also difficult to implement in an outpatient primary setting.

Each patient will be included in one of the following meglumine antimoniate treatment groups per IM route:

1. 20mg Sb5 + / kg / day for 20 days
2. 5mg Sb5 + / kg / day for 30 days

There will be no cross-over between the groups for the purposes of this study. The data of those patients who need a definitive interruption of a regimen will be analyzed according to the group to which they were randomized, which means, by intention to treat. Data collection will take place according to the consultation schedule.

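### A 7.13 withdraws patients from the study for pregnancy, a new immunosuppressive or toxic drug, or unrelated Grade 3 disease, with no time limit and no statement that outcome visits continue to days 360 and 770

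*Protocol*

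**What the plan says.** The protocol has two separate lists. A 7.12 gives the criteria for stopping study treatment for good. A 7.13 is headed "Criteria for withdrawal from the study (but not excluded from data analysis". Its criterion 2 is pregnancy, criterion 3 is "need for introduction of immunosuppressive or potentially toxic drug (chemotherapy for cancer, tuberculosis or leprosy scheme", and criterion 4 is "Intercurrent disease, unrelated to the drug studied, but with manifestations equivalent or superior to clinical AD Grade 3". None of the three is limited to the treatment period. Criterion 6 is the patient's own decision not to continue.

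A 7.2 sets the two courses: "20mg Sb5 + / kg / day for 20 days" and "5mg Sb5 + / kg / day for 30 days". In A 7.6.1 the late outcomes include "disappearance of erythema until the consultation on day 360 (definitive cure" and "no appearance of mucosal lesion until the consultation of day 770".

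On analysis, A 7.2 says that patients whose regimen is definitively interrupted are analysed as randomised, and then: "Data collection will take place according to the consultation schedule". A 7.17 sets an intention-to-treat analysis, with a per-protocol analysis of the primary endpoint as a supplement.

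**The concern.** A patient can complete the course, heal, and then meet criterion 2, 3 or 4 at, say, day 200. No study drug is being given and the late outcomes can still be observed. On its wording, A 7.13 takes this patient out of the study before definitive cure and mucosal status are read.

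Staying in the analysis population does not supply an outcome. If visits stop, an intention-to-treat comparison at day 360 or day 770 includes patients whose result nobody recorded, and the result depends on how those gaps are filled. Carrying an earlier cure forward would hide any later failure. Scoring the gap as failure would add failures that do not come from the regimen. Whether patients keep attending visits is decided by the protocol, and an analysis plan cannot recover visits that did not take place.

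**Working it through.** **1. Does the rule reach past the treatment course?**
- Criteria 2 to 4 appear in the A 7.13 list and not in the A 7.12 list, so they are worded as study withdrawal and not only as stopping treatment.
- Criterion 5 of the same list covers re-treatment after poor initial or late response. A 7.6.1 reads late response from day 140 onward, so the list plainly operates after dosing has ended.
- No criterion has an end date. On the wording, criteria 2 to 4 apply up to day 770.

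**2. Do other sections secure the later visits?**
- The A 7.13 heading and A 7.17 settle who is analysed. Neither says that outcomes are still collected.
- The A 7.2 sentence on data collection follows a sentence about interrupted regimens. It does not mention patients who finished treatment and were withdrawn later.
- A 7.10 offers active search to patients who miss an appointment. It does not say whether a withdrawn patient still has appointments.

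**3. How much follow-up is exposed?** Using the longer, 30-day course:
- to day 360: (360 − 30)/360 = 91.7%
- to day 770: (770 − 30)/770 = 96.1%

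These are shares of calendar time, not of information lost. Whatever was recorded before the event stays in the analysis.

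**4. Possible loss.** The protocol gives no rate for these events, so there is no figure of its own to reproduce. Assumption: 3%, 5% or 10% of patients per year meet criteria 2 to 4 after day 30, and visits then stop. Proportion without an outcome at day D = 1 − exp(−rate × (D − 30)/365); multiply by 36 for patients per arm.

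| Rate per year | Day 120 | Day 360 | Day 770 |
|---|---|---|---|
| 3% | 0.7% (0.3) | 2.7% (1.0) | 5.9% (2.1) |
| 5% | 1.2% (0.4) | 4.4% (1.6) | 9.6% (3.5) |
| 10% | 2.4% (0.9) | 8.6% (3.1) | 18.4% (6.6) |

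Initial cure at day 120 is barely touched.

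**5. Possible effect on power (illustration only).** The protocol states no expected cure rate. With equal rates p, one-sided 5% and 80% power, n per arm = (1.645 + 0.842)² × 2p(1 − p)/0.15². At p = 0.93 this is 6.18 × 0.1302/0.0225 = 35.8, so the planned 36 is reached with an assumed cure rate near 93%. Power = Φ(0.15/√(2p(1 − p)/n) − 1.645).
- No loss, n = 36: 80.2%.
- 5% lost in both arms: 78.4% if the outcomes are dropped (n = 34.2); 63.3% if they are kept as failures (p = 0.93 × 0.95 = 0.8835, n = 36).
- 10% lost in both arms: 76.5% if dropped (n = 32.4); 53.1% if kept as failures (p = 0.837, n = 36).

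The protocol states neither handling rule. The figures show that the handling would matter more than the number of patients lost.

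**The case against.** The strongest reply is that the protocol does not mean to lose these patients. The heading of A 7.13 keeps them in the analysis, A 7.2 ties data collection to the consultation schedule, A 7.10 provides active search, and A 7.15.1 lists keeping missing data low among the items to monitor. This stands against one tempting inference, that definitive-cure and mucosal outcomes are discarded. No section orders that, and outcomes already recorded are kept. It does not close the gap, because no section says that a patient withdrawn from the study keeps attending.

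The size is also open to challenge. The yearly rates are assumptions with no anchor in the document. Criterion 2 can apply only to women, and A 7.4.2 excludes women without adequate contraception. A reader might set the largest loss, 6.6 patients per arm, beside the margin of 0.15 × 36 = 5.4 patients. That comparison is not valid: the margin is a difference between arms, and nothing in the document suggests that these events would differ by arm after treatment. By its own wording, criterion 4 is unrelated to the drug.

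A reader might also argue that the loss is informative because immunosuppression could bring reactivation. The document gives no support for that link, and the point does not need it. Finally, the choice of imputation may be set out in an analysis plan that is not shown, so its absence here is not a finding.

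**Conclusion.** The point holds as a conflict between a conduct rule and the planned analysis. A 7.13 makes three events grounds for leaving the study, with no time limit, while the intention-to-treat analysis needs outcomes at day 360 and day 770. Later outcomes of patients who completed treatment may go uncollected; the protocol neither secures them nor orders them dropped.

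The size is unknown. On the assumed 3% to 10% per year, and only if visits do stop at withdrawal, about 3% to 9% of patients would lack a day-360 outcome and 6% to 18% a day-770 outcome. The day-770 mucosal outcome is the most exposed. This is worth correcting because the remedy is cheap. It does not show that the trial's conclusion would be wrong.

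**What to change.** Reconcile A 7.13 with A 7.2 and A 7.17 in one paragraph:
- meeting criterion 2, 3 or 4 does not end outcome follow-up;
- the event and its date are recorded;
- the patient stays on the A 7.6.1 visits to day 770 unless the patient withdraws from continuing in the study (criterion 6).

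The paragraph should deal with follow-up only. When study drug stops is a clinical matter for the investigators and is not part of this point.

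The cost is a short amendment and the attendance of a few patients at visits already on the schedule. The small downside is that some outcomes will be observed under concomitant drugs; with the event dates recorded, a sensitivity analysis can flag them.
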